# **Informed consent**

A written informed consent will be obtained from eligible participants. Voluntary informed participation and freedom of refusal at any time during study will be applied strongly. Participants can withdraw from the study anytime without giving reason and fear. Privacy and confidentiality of the collected information will be ensured at all levels. The purpose of the study, benefits, and harm to the participants will be properly explained in simple and understandable terms by the enumerator.

# **Budget**

| **Proposed Budget for the study** | | | | | | | **Justifications** |
| --- | --- | --- | --- | --- | --- | --- | --- |
| **S.N.** | **Description** | **Person** | **Months** | **LOE (%)** | **Rate NRs.** | **Total Amount (NRs.)** |  |
| **A** | **Personal Cost** |  |  |  |  |  |  |
| A1 | Principal Investigator | 1 | 14 | 0.3 | 2,500 | 10,500 | Since both principal investigator and Co-Investigators are full-time faculty at Asian College for Advance Studies, we have allocated minimum cost that includes minimum allowances to cover their necessary expenses. |
| A2 | Co-Investigator | 1 | 14 | 0.3 | 2,500 | 10,500 |  |
| A3 | Thesis writing students | 2 | 3 | 0.5 | 4,000 | 10,000 | This cost covers the minimum remuneration for thesis writing students who will involve in this study and work as an enumerators |
| A4 | Dietitian fee | 1 | 3 | 0.5 | 4,000 | 6,000 | Dietitian will be provided with a minimum fee for the patients counseling and diet plan to the study participants |
|  | **Sub-total** |  |  |  |  | **37,000** |  |
| **B** | **Laboratory cost** | **Person Items** | **Unit** |  | **Unit Cost** | **Total Amount** |  |
| B.1 | Bio-chemical test (testing service cost) | 156 | 2 |  | 600 | 202,800 | This cost covers the Biochemical tests charge during baseline, midline and end line. |
| B2 | Stadiometer | 2 | 1 | 1 |  |  | This equipment will be provided by Asian College For Advance Studies |
| B3 | Weighing Machine | 2 | 1 | 1 |  |  | This equipment will be provided by Asian College For Advance Studies |
| B4 | BP Set | 2 | 1 | 1 | 2,500 | 5,000 | This equipment will be provided by Asian College For Advance Studies |
|  | **Sub-total** |  |  |  |  | **207,800** |  |
| **C** | **Field Cost** | **Person** | **Days** | **Times** | **Unit Cost** | **Total Amount** |  |
| C1 | Travel cost | 2 | 72 | 1 | 100 | 14,400 | This cost is allocated for enumerator travel costs during the data collection period. |
| C2 | Daily allowances | 1 | 72 | 1 | 200 | 14,400 | Daily allowances for enumerators during the data collection period |
| C3 | Survey cost (tools pretesting) | 1 | 1 | 1 | 20,000 | 20,000 | Cost for tools pre-testing (Data collection tools, IEC materials, and menu plan sheet pre-testing ) |
|  | **Sub-total** |  |  |  |  | **48,000** |  |
| **D** | **Office cost** | **Event** | **Days** | **Times** | **Unit Cost** | **Total Amount** |  |
| D1 | Communication fee | 1 |  | 1 | 10,000 | 10,000 | This cost will cover the communication charge occurred during the study period |
|  | **Sub-total** |  |  |  |  | **10,000** |  |
| **E** | **Consultation services** | **Unit** | **Days** | **Times** | **Unit Cost** | **Total Amount** |  |
| F1 | Questionnaire, Nutrition Education Module, Diet plan sheet design, and sharing meeting | 1 | 1 | 1 | 20,000 | 20,000 | This cost is allocated for tools to develop, finalization meeting sharing workshop with study team and concern experts. |
| F2 | Workshop consultation on nutrition education module and diet plan among Dietitian | 1 | 4 | 1 | 5,000 | 20,000 | This cost is allocated for workshop consultation meeting for the approval of NEC and diet plan by multi-disciplinary expert team |
| F3 | Enumerators training/orientation | 6 | 1 | 1 | 1,000 | 6,000 |  |
| F4 | Data analysis | - | - | - | - | - | Analyzed by PI and CO-PI, therefore no cost is allocated. |
|  | **Sub-total** |  |  |  |  | **46,000** |  |
| **G** | **Students support** | **Person** | **Items** | **Times** | **Unit Cost** |  |  |
| G1 | Thesis Proposal preparation cost | 2 | 1 | 1 | 2,500 | 5,000 | This cost is provided to the students for their thesis proposal preparation |
| G2 | Thesis Preparation Cost | 2 | 1 | 1 | 2,500 | 5,000 | This cost is provided to the students for their thesis report preparation |
|  | **Sub-total** |  |  |  |  | **10,000** |  |
|  | **Total ( A+B+C+D+E+F+G)** |  |  |  |  | **358,800** |  |
| H | **Facilities and Administration Cost** |  |  |  |  |  |  |
|  | Overhead cost (10%) |  |  |  |  | 35,800 |  |
|  | **Sub-total** |  |  |  |  | **35,800** |  |
|  | **TOTAL STUDY COST without NHRC fee** |  |  |  |  | **394,680** |  |
|  | **NHRC (Ethical clearance) Fee 3%,** | **1** |  |  |  | **5,320** |  |
|  | **Grand Total** |  |  |  |  | **400,000** | **In words: Four lakhs only** |
|  |  |  |  |  |  |  |  |

**Main Study Questionnaire in English - Baseline/End line**

| **Participants Information** | | | |
| --- | --- | --- | --- |
|  | Response | | Code |
| Study Group | Control 0  Intervention 1 | |  |
| Date |  | |  |
| Participants ID |  | | I1 |
| Participants full name |  | | I2 |
| Contact number |  | | I3 |
| Baseline interview date |  | | I4 |
| Follow-up date |  | | I5 |
| End line interview date |  | | I6 |
| Consent has been read and obtained | Yes  No | 1  2  If no, End | I7 |
| **Section 1: Socio-demographic information, Baseline** | | | |
| Sex ( record male/female as observed) | Male  Female | 1  2 | C1 |
| How old are you | …….years |  | C2 |
| What is your education level? | No formal education  Primary (1-5)  Secondary (6-10)  Higher secondary(11-12)  Bachelors and above  Refused | 1  2  3  4  5  88 | C3 |
| What is your ethnic background?  (Refer to caste classification: CC1 ) | Dalit  Disadvantaged Janajati  Relatively advantaged Janajati  Disadvantaged Non-dalit Terai caste group  Religious minorities  Upper caste group  Others  Refused | 1  2  3  4  5  6  7  88 | C4 |
| What is your religion? | Hindu  Buddhist  Muslim  Kirat  Christian  Others  Refused | 1  2  3  4  5  6  88 | C5 |
| What is your marital status? | Never married  Married  Separated/divorced  Widowed  Cohabiting  Refused | 1  2  3  4  5  88 | C6 |
| Which of the following best describes your main occupation? | Government employee  Non-government employee  Self-employed  Students  Homemaker  Retired  Unemployed  Others  Refused | 1  2  3  4  5  6  7  8  88 | C7 |
| Where do you live? | Urban  Rural | 1  2 | C8 |
| How much is your average monthly Income? | Rs | ……… | C9 |
| Family history of Diabetes Mellitus | Yes  No | 1  2 | C10 |
| **Section 2: Behavioral information Baseline/Endline** | | | |
| **Tobacco use** | | | |
| Do you currently smoke any tobacco products, such as cigarettes, bidis, cigars, pipes, hukahs, or tamakhus? | Yes  No | 1  2  If No, go to A1 | T1 |
| How frequently do you smoke tobacco products? | Daily  5-6 days a week  3-4 days a week  1-2 days a week  Occasionally | 1  2  3  4  5 | T2 |
| In the past, did you ever smoke any tobacco products? | Yes  No | 1  2  If No, go to A1 | T3 |
| In the past, how frequently did you smoke tobacco products? | Daily  5-6 days a week  3-4 days a week  1-2 days a week  Occasionally | 1  2  3  4  5 | T4 |
| **Alcohol consumption** | | | |
| Have you **ever** consumed an alcoholic drink such as beer, wine, spirits fermented cider or *jaad, chyang, raksi, aila or tungba?* | Yes  No | 1  2  If No, go to P1a | A1 |
| Have you consumed an alcoholic drink within the past 12 months? | Yes  No | 1  2 | A2 |
| During the past 12 months, how frequently have you had at least one standard alcoholic drink? | Daily  5-6 days per week  3-4 days per week  1-2 days per week  1-3 days per month  Less than once a month | 1  2  3  4  5  6 | A3 |
| **Section 3: Physical and biochemical measurement** | | | |
| Blood pressure |  |  |  |
| Reading 1 | Systolic (mmHg) | ……. | P1a |
|  | Diastolic (mmHg) | ……. | P1b |
|  | Beats per minute | ……. | P2a |
| Reading 2 | Systolic (mmHg) | ……. | P4a |
|  | Diastolic (mmHg) | ……. | P2b |
|  | Beats per minute | ……. | P4b |
| Reading 3 | Systolic (mmHg) | ……. | P3a |
|  | Diastolic (mmHg) | ……. | P4b |
|  | Beats per minute | …… | P4c |
| **Height, weight, waist and Hip Circumference** | | | |
| Height | in centimeter (cm) | …….. | P5 |
| Weight | in kilograms (kg) | …….. | P6 |
| Waist Circumference | in centimeter (cm) | …….. | P7 |
| Hip circumferences | in centimeter (cm) | …….. | P8 |
| **Biochemical measurements** | | | |
| HbA1c | % | ........ | P9 |
| FBS | mg/dL | …… | P10 |
| Total cholesterol | mg/dL | …… | P11 |
| Triglycerides | mg/dL | …… | P12 |
| LDL | mg/dL | …… | P13 |
| HDL | mg/dL | …… | P14 |
|  |  |  |  |
| **Current medication used** | | | |
|  |  |  | M1 |
|  |  |  | M2 |
|  |  |  | M3 |
|  |  |  | M4 |
|  |  |  | M5 |
|  |  |  | M6 |
|  |  |  | M7 |
|  |  |  | M8 |
|  |  |  | M9 |
|  |  |  | M10 |
|  |  |  | M11 |
|  |  |  | M12 |
|  |  |  | M13 |
|  |  |  | M14 |

**Section 4: A 24 hour recall, Baseline/End line**

|  | **Items** | **Description of food or drinks** | **Household amount** | **Amount (g or ml)** | **Preparation/ingredients** |
| --- | --- | --- | --- | --- | --- |
| **Breakfast** |  |  |  |  |  |
|  |  |  |  |  |  |
|  |  |  |  |  |  |
|  |  |  |  |  |  |
|  |  |  |  |  |  |
|  |  |  |  |  |  |
|  |  |  |  |  |  |
| **Lunch** |  |  |  |  |  |
|  |  |  |  |  |  |
|  |  |  |  |  |  |
|  |  |  |  |  |  |
|  |  |  |  |  |  |
|  |  |  |  |  |  |
|  |  |  |  |  |  |
|  |  |  |  |  |  |
|  |  |  |  |  |  |
|  |  |  |  |  |  |
| **Snacks/mid-day** |  |  |  |  |  |
|  |  |  |  |  |  |
|  |  |  |  |  |  |
|  |  |  |  |  |  |
|  |  |  |  |  |  |
|  |  |  |  |  |  |
|  |  |  |  |  |  |
|  |  |  |  |  |  |
|  |  |  |  |  |  |
|  |  |  |  |  |  |
|  |  |  |  |  |  |
| **Dinner** |  |  |  |  |  |
|  |  |  |  |  |  |
|  |  |  |  |  |  |
|  |  |  |  |  |  |
|  |  |  |  |  |  |
|  |  |  |  |  |  |
|  |  |  |  |  |  |

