## **Specific objectives:**

- To measure the change in HbA1c level among T2DM patients between the intervention and control/usual care arm.
- To evaluate the change in macronutrient intake level among T2DM patients in the intervention and usual care arm.
- To assess dietitian-led nutrition education and counseling on nutritional knowledge of diabetes among T2DM patients.
- To evaluate the change in biochemical parameters among T2DM patients in the intervention and usual care arm.
- To assess the nutritional status such as BMI and WHR among T2DM patients

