## **7.10. Tools and techniques for data collection**

The baseline and end-line data collection will be performed in both intervention and usual care arm. A pre-tetsed culturally accepted and adapted, Nepali translated version tools and techniques will be used to conduct the study. A total of three data collection team who have graduated in health or nutrition science will be hired from the local area.

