**Tools and procedure**

- Screening checklist: This checklist entails information regarding inclusion and exclusion criteria.
- Baseline questionnaire: The study participants’ information on Socio-demographic, such as age, sex, occupation, educational level, residence, religion, ethnicity, etc. will be taken by using a face-to-face structured questionnaire interview. The questionnaire will be adopted from NDHS 2017 and STEP Survey 2019^22,23^.
- Dietary intake: Dietary intake assessment will be assessed before intervention (baseline) and after intervention (end line) using 24-hour qualitative dietary recall and food frequency questionnaire (FFQ) to compute the macronutrient intake level.
- Biochemical measurements: A fasting blood sample for HbA1c, fasting glucose, liver function test (bilirubin, ALT, AST ALP, and albumin) and lipid profile (total cholesterol, triglycerides, HDL, LDL) will be measured at baselines, three months and six months. All blood samples will be taken and handled, analyzed and disposed of according to local practice policy.
- Quality of life: The Problem Areas in Diabetes (PAID) score^24^, a 20 items questionnaire measuring the problems related to emotions, treatment, food and social support, will be measured at baselines and 12 months.
- Physical measurement: Height will be measured using a stadiometer to the nearest 1cm. Participants' weight will be measured to the nearest 0.1kg using the Seca weighing scale. BMI will be measured calculated using the widely used formula (BMI= weight (kg)/height (m)^2^), and waist Hip Circumference (WHR) will be measured using measuring tape. Systolic and diastolic blood pressure will be measured three times after 5 minute seated rest using a sphygmomanometer and stethoscope. The trained data enumerator will be taking physical measurements according to the study manual procedures.
- Nutritional knowledge score on diabetes: The diabetes knowledge test (DKT)^25^will be used to assess the nutritional knowledge score on diabetes.
- Physical activity: The physical activity will be measured using the Global Physical activity questionnaire recommended by WHO STEPwise surveillance tools^23^.
- Monitoring checklist: This will be used as every month follow up checklist. The information on lifestyle modification such as consumption of food, physical activities, adherence, and diabetic-related minor and major complication will be sought.

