In the second phase, all patients in the intervention arm will be provided an individualized diet plan to reinforce the concept of controlling the serving size of foods every month which will be lasted for 45-60 minutes. During the patient's visits to OPD, the dietitian will obtain daily nutrient intake by asking the patients to recall the foods and beverages consumed for the past 24 hours. Each participant will be given an individual basis diet plan within the limit of the acceptable macronutrient distribution range (AMDR) ^20^. Energy requirements will be prescribed by a dietitian for each participant based on the patient's height, weight, and physical activity level according to the guidelines of the American diabetic association (ADA)^26^. Energy distribution will be set in accordance with the limit of AMDR i.e. protein 10-35%, fat 20-35%, and carbohydrate 45-65%)^20^. This guideline will be developed for the Nepalese population based on the ADMR compositions includes the use of a food exchange portion in diabetic diet planning. One piece of food exchange portion is defined as one serving for every 80 kcal of a food product. Thus, a similar type of food exchange portion can be exchanged where the nutritional value is almost the same. The individual total energy required per day is calculated according to the individual weight and daily physical activity level using Harris-Benedict equations. Balanced diet for each patient will be planned and the total day's diet plan is distributed into five meal patterns such as breakfast, launch, snack, and dinner and a bedtime snack. In order to avoid excessive energy intake and assure a balanced diet, we emphasize moderate carbohydrates, moderate fat foods and consuming foods rich in fiber and micronutrients. Follow up will be done every month. All educational materials will be developed in English and then translated into Nepalese language.

Table 1 Content of Nutrition Education and Counseling Module for DIAM-D trial

| SN | Topic | Module |
| --- | --- | --- |
| 1 | Knowledge about diabetes mellitus | Basic concept of nature of diabetes, causes and risk factors, types, clinical features, insulin action, body response to food in diabetes and non-diabetes state and complication |
| 2 | Treatment of diabetes | Diet alone, diet and drugs or diet and insulin, exercise and their  role in treatment of diabetes |

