# **Limitations of the study**

In this study, the participants will be enrolled from OPD basis, so, we cannot resolve the adherence of dietary advice to all participants. Similarly, there may be a recall bias to collect 24-hour dietary recall and may have social desirability bias for collecting behavioral related history. To minimize recall bias, proper probing will be carried out. Likewise, interviewer bias can occur, to minimize it the length of time taken to interview the average intervention and the average control will be noted. Selection bias can occur during the selection process. We will strongly follow randomization to the selection of intervention and usual care arms by a trained data enumerator so that this will minimize the confounding. Also, the cross-contamination may occur between intervention and control arms. We will suggest the participants from the intervention arm not to share the provided information with the others to prevent cross contamination.

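### The 24-hour recall form has no prompt for the bedtime snack in the intervention diet plan, which risks unequal under-recording of macronutrient intake between the arms (minor)

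*Protocol*

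**What the plan says.** **Diet plan.** Section 7.11 describes the individual plan for the intervention arm. The day's food is "distributed into five meal patterns such as breakfast, launch, snack, and dinner and a bedtime snack". The same section gives usual care as routine care, with no meal plan of this kind.

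**Recall form.** Dietary intake is recorded in "Section 4: A 24 hour recall, Baseline/End line". The form has four labelled blocks: breakfast, lunch, "Snacks/mid-day" and dinner. Blank rows follow each label, with free columns for item, description, household amount, weight or volume, and preparation. No block is labelled for bedtime, after dinner or other occasions.

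**Who is measured.** Section 7.10 states: "The baseline and end-line data collection will be performed in both intervention and usual care arm". The same form therefore serves both arms.

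**What it feeds.** One specific objective is: "To evaluate the change in macronutrient intake level among T2DM patients in the intervention and usual care arm". Macronutrient intake also stands in the general objective and the hypothesis. Section 7.10 names the tools as "24-hour qualitative dietary recall and food frequency questionnaire (FFQ) to compute the macronutrient intake level". The primary outcome in the project summary is HbA1c.

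**Safeguard.** Under the limitations the protocol says: "To minimize recall bias, proper probing will be carried out". It does not say what the probes are.

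**The concern.** A recall form's headings are the interviewer's prompts, and an occasion that is not asked about depends on the participant to volunteer it. Here the headings cover four of the five occasions in the trial's own diet plan, and the fifth is prescribed in one arm only.

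That makes it more than general recall error. Before randomisation both arms should lose after-dinner food about equally. After it, one arm has been told to eat a bedtime snack and the other has not. Any extra loss would then appear at end line and not at baseline, so subtracting baseline would not remove it. It would lower recorded energy and macronutrients in the intervention arm, a direction that could be taken for a dietary effect.

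At stake is the between-arm comparison of macronutrient intake.

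**Working it through.** The protocol gives no figure for this point, so there is none to reproduce. The check is a comparison of texts, followed by bounds on assumed inputs.

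**Step 1. Plan against form**

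| Occasion in the diet plan (7.11) | Labelled block on the recall form (Section 4) |
| --- | --- |
| Breakfast | Breakfast |
| Lunch | Lunch |
| Snack | Snacks/mid-day |
| Dinner | Dinner |
| Bedtime snack | None |

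Four of five occasions have a prompt. The fifth can be written in the blank rows under Dinner or, on a broad reading of the label, in the snack block. There is room for it, but nothing asks for it.

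**Step 2. Form of the possible bias**

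Let k be the energy of a bedtime snack. Let f_int and f_ctrl be the shares of each arm whose snack is eaten on the recall day but written nowhere. Then

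bias in (intervention - control) recorded energy = -(f_int - f_ctrl) × k.

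- From the protocol (7.11): one food exchange is 80 kcal.
- Assumed: the snack is one or two exchanges, so k = 80 to 160 kcal.
- Not given anywhere: f_int and f_ctrl. The range 0 to 1 is taken for their difference.

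| f_int - f_ctrl | k = 80 kcal | k = 160 kcal |
| --- | --- | --- |
| 0 (always recorded, or missed equally) | 0 | 0 |
| 0.5 | -0.5 × 80 = -40 | -0.5 × 160 = -80 |
| 1 (eaten by all and never recorded in one arm, no loss in the other) | -80 | -160 |

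If controls lose more after-dinner food than the intervention arm, the sign reverses.

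**Step 3. Scale**

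On an assumed 1500 to 2000 kcal/day, a snack is between 80/2000 = 4.0% and 160/1500 = 10.7% of daily energy.

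Section 7.8 lists carbohydrate, fat and protein rather than energy. If the snack has the plan's own 45-65% of energy from carbohydrate (an assumption), the carbohydrate energy in one unrecorded snack is between 0.45 × 80 = 36 kcal and 0.65 × 160 = 104 kcal.

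**Step 4. Other tools that might catch the snack**

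- The food frequency questionnaire is named in 7.10, but no such section appears in the questionnaire supplied. It may exist separately. How it is combined with the recall is not stated, so it cannot be counted on to restore a missed snack.
- Probing is promised in general terms only. The trial is open-label and the questionnaire's first field is the study group, so interviewers may know the arm when they decide how far to probe.

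**The case against.** The strongest reply is that a missing label is not a missing place. The form is an open 24-hour grid with blank rows after every heading, including Dinner, and nothing restricts entries to the named meals. The label for the snack block can be read as snacks in general. The protocol also plans a data collection manual, a week of training, pre-testing, and revision of the questionnaire afterwards. **This stands** against any statement that the snack cannot be recorded. It does not supply the prompt, because none of these provisions mentions food after dinner.

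A second reply concerns direction. Intervention participants go over their diet with a dietitian, including a 24-hour recall at clinic visits, and may volunteer a bedtime snack more readily than controls. Controls may also eat after dinner. **This stands too:** the direction is plausible, but the documents do not establish it.

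A reader might infer that end-line intake is in fact under-recorded in the intervention arm, and that the comparison's false-positive rate is inflated. Figures can be produced. With 54 per arm and an assumed SD of change in recalled energy of 400-600 kcal, a two-sided 5% t-test would reject in 11-18% of trials at a pure recording bias of 80 kcal, and in 28-54% at 160 kcal. A bias of 40 kcal gives 6-8%. The arithmetic is right, but the documents do not support the inference. The SD, the snack size and the one-sided omission are all assumed. The 80 and 160 kcal cases, taken as one or two exchanges, need every intervention participant to eat the snack on the recall day, none of it to be recorded, and controls to lose nothing comparable. The lower end is no bias and the nominal 5%.

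**Conclusion.** The mismatch between plan and form is real. The recall form prompts for every occasion in the intervention diet plan except the bedtime snack, which only that arm is prescribed. This leaves a risk of differential under-recording of end-line macronutrient intake.

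Whether any bias occurs, and how large it is, cannot be settled from the protocol. The range of 0 to -160 kcal/day in the between-arm energy difference rests on an assumed one- or two-exchange snack and on omission at least as common in the intervention arm as in usual care. Zero is a possible value.

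Severity is minor. The point touches a stated objective and leaves HbA1c, a laboratory value, unaffected. It is worth acting on because a snack that was not asked about cannot be recovered after the interview.

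**What to change.** Add two labelled blocks to Section 4 of the questionnaire: Bedtime / after dinner, and Any other eating occasion. Instruct interviewers, in the data collection manual and in training, to read every block aloud to every participant, in both arms, at baseline and at end line. Identical wording across arms and time points is what guards against an arm-related difference.

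The change concerns recording only and leaves the diet plan as it is. It can be made in the revision already planned after pre-testing. The cost is two form rows and about a minute per interview, with no extra visits or staff.
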